### Economic evaluation/ cost analysis

The economic evaluation will be performed according to the Dutch guidelines of the national health care institute [31]. As mentioned earlier, the study will include 1200 patients in the intervention group and 1200 patients in the control group. As it is impossible to follow each patient, during 1 year follow-up we will use intermittent data collection instead of continuous data collection, because results showed that the best estimations of annual impact can be obtained by random cohort data collection, using 3 random cohorts, enduring that at least a third of the participants will be measured at each measured point [31]. Intermittent measurement combined with individual mean (IM_ imputation) will be used to calculate the annual costs per Quality Adjusted Life Years (QALYs). This means that at each measurement point 400 patients per group will complete the RUM instrument for the costs and EQ-5D-5L for the QALYs during every three – 6 months after inclusion.

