#### Secondary outcomes

The secondary outcomes of this study are (I) mortality within 1 year after study inclusion; (II) the number of emergency department visits; (III) the number of nursing home admissions; (IV) time to hospital readmission; and (V) the number of hospital readmissions after 30 and 180 days. Next, we will analyze whether the readmission is (probably) medication-related. Whether a hospital readmission is medication-related will be defined afterwards, using the triggerlist. The information for secondary outcomes will be obtained from the electronic prescription system and electronic patient record. Furthermore, quality of life (QoL) and costs measured from a societal perspective will be assessed at baseline (hospital discharge) and after 3, 6 and/or 12 months (see questionnaires).

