## Discussion

This study is expected to add evidence on the knowledge of medication optimization and whether continuous use of a CDSS ameliorates the risk of hospital readmission and other adverse outcomes in older patients who have already had an unplanned hospitalization.

Hospital (re)admissions place a significant burden on the healthcare system, with impact on quality of life from the patient perspective and being an important cost driver from the societal perspective. In earlier studies, different interventions have been investigated to reduce readmissions, but the results were inconclusive due to large heterogeneity in study designs and therefore their effect on hospital readmissions. As such, the optimal template of medication optimization is still unknown. This is the first study that includes patients with a high risk of having a medication-related admission based on the triggerlist. We deliberately chose to include all readmissions as primary outcome and not specifically medication-related readmissions because a clear definition is lacking. By using a suboptimal definition it is likely we would miss readmissions that later turn out to be medication-related.

To our knowledge, this is the first large randomized blinded study providing one-year follow-up data and reporting not only on quality of care indicators (readmissions), but also on quality-of-life and costs. This contrasts to other studies in the field, which usually have a follow up of 30 or 60 days at most. This is an important strength of our study, while we believe that in this population healthcare status and medication prescriptions alter frequently and a follow up of only 30 or 60 days is too short to identify all possible consequences and the time to the occurrence of adverse outcome might vary considerably. Another strength of this study is that it will be conducted in the outpatient setting and directly in daily clinical practice and therefore improves the possibility to implement the CDSS in the shortest possible notice. The inclusion of patients has already started in April 2019, but the patient inclusion was slower than expected due to different causes. The participation of GPs and pharmacists was lower than expected, we experienced several IT problems (not related to CDSS itself) that affected inclusion and from March 2020 we had to deal with the COVID-19 pandemic. As such, during many months the inclusion was discontinued.

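### Hospital readmissions are costed from one follow-up form per patient because patients supposedly cannot be followed for a year, yet the trial already records readmission over that year; for this component the form has about 2.2 to 4.7 times the variance

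*Protocol article*

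**What the plan says.** Under Economic evaluation/ cost analysis, the protocol article states that "the study will include 1200 patients in the intervention group and 1200 patients in the control group" and continues: "As it is impossible to follow each patient, during 1 year follow-up we will use intermittent data collection instead of continuous data collection". It cites a source in favour of random-cohort collection, "using 3 random cohorts, enduring that at least a third of the participants will be measured at each measured point", and specifies that "at each measurement point 400 patients per group will complete the RUM instrument for the costs and EQ-5D-5L for the QALYs". Annual costs are to be obtained by individual mean imputation. The Questionnaires section adds that every patient gets a RUM at discharge and a second one at 3, 6 or 12 months.

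Other sections describe year-long follow-up. The primary outcome is readmission within 1 year of inclusion. The secondary outcomes include emergency department visits, nursing home admissions, time to readmission and readmissions after 30 and 180 days, and "The information for secondary outcomes will be obtained from the electronic prescription system and electronic patient record". The Discussion describes hospital (re)admissions as "being an important cost driver from the societal perspective".

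No section says that the recorded admissions or visits will be valued in the cost analysis.

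**The concern.** The reason given for sampling is that patients cannot be followed through the year. For readmissions, the trial does exactly that in order to measure its primary outcome. Readmission is also the event that the decision support system is meant to reduce, so part of any cost difference should arise there. If that component is estimated from a fraction of each patient's year and scaled up, although the record covers the whole year, the readmission part of the cost comparison becomes noisier for no stated gain. The trial could then show fewer readmissions in its effect analysis while the cost analysis is too imprecise to show the matching saving.

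**Working it through.** **Inputs from the protocol article.** 1200 patients per group, three cohorts and 400 per group per time point (Economic evaluation); 20% versus 15% readmitted within a year (Sample size calculation); one follow-up RUM at 3, 6 or 12 months (Questionnaires). The plan's own figure reproduces: 1200/3 = 400.

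**Assumptions not in the article.** At most one readmission per patient, spread evenly over the year; every form returned; a recall window of 3 to 6 months. The recall length is not stated. Three and 6 months are the gaps between the measurement points.

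**Full-year record.** The variance of the difference in mean annual readmissions is [0.20×0.80 + 0.15×0.85]/1200 = 0.2875/1200, so SE = 0.0155.

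**One window of w months per patient, scaled by k = 12/w.** The per-patient variance is v(p) = k²(p/k)(1 − p/k).
- w = 3, k = 4: 16×0.05×0.95 + 16×0.0375×0.9625 = 0.7600 + 0.5775 = 1.3375. SE = √(1.3375/1200) = 0.0334; variance ratio 1.3375/0.2875 = 4.7.
- w = 6, k = 2: 4×0.10×0.90 + 4×0.075×0.925 = 0.3600 + 0.2775 = 0.6375. SE = √(0.6375/1200) = 0.0230; variance ratio 0.6375/0.2875 = 2.2.

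**Three cohorts of 400 with different windows.**
- Windows of months 0–3, 3–6 and 6–12, cohort means added: [2×(0.0475 + 0.03609) + (0.0900 + 0.069375)]/400 = 0.32656/400. SE = 0.0286; ratio 3.4.
- The same windows, each patient scaled to a year and the three cohorts averaged, which is closer to individual mean imputation: (1.3375 + 1.3375 + 0.6375)/3 = 1.1042. SE = √(1.1042/1200) = 0.0303; ratio 3.8.
- Each form reaching back to inclusion (3, 6 and 12 months), scaled and averaged: (1.3375 + 0.6375 + 0.2875)/3 = 0.7542. SE = √(0.7542/1200) = 0.0251; ratio 2.6.

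With power = Φ(0.05/SE − 1.96) for the 5-point difference:

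| Source | SE | Variance ratio | 0.05/SE | Power |
|---|---|---|---|---|
| Full-year record | 0.0155 | 1 | 3.2 | about 90% |
| 6-month window | 0.0230 | 2.2 | 2.2 | about 58% |
| Windows 0–3, 3–6, 6–12, added | 0.0286 | 3.4 | 1.7 | about 42% |
| 3-month window | 0.0334 | 4.7 | 1.5 | about 32% |

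The power column describes only how visible the readmission difference is in the cost data. It is not the power of the primary analysis.

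**Check under another model.** Allow repeat admissions as a Poisson process with P(at least one in a year) = 0.20, so the control rate is −ln 0.80 = 0.223 per year. Over 1200 patients the record holds 1200×0.223 ≈ 268 control-group admissions. Three-month windows see 268/4 ≈ 67; windows 0–3, 3–6 and 6–12 in cohorts of 400 see 400×0.223 ≈ 89. The form keeps 25% to 33% of the information on admission cost. In simulation with strong differences in risk between patients (gamma frailty, shape 0.25) it keeps 35% to 46%.

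**Total societal cost.** Let h be the hospital share of the form-based variance, r the inflation of the hospital part (3 to 4 in the Poisson model) and the components independent. The form then keeps (1 − h) + h/r of the information, and the SE ratio is the square root of its inverse.

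| h | Information kept | SE, form versus records |
|---|---|---|
| 30% | 77–80% | 1.12–1.14 |
| 50% | 62–67% | 1.22–1.26 |
| 70% | 48–53% | 1.37–1.45 |
| 90% | 32–40% | 1.58–1.75 |

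More than half is lost only if h exceeds 0.5/(1 − 1/r), which is 67% for r = 4 and 75% for r = 3.

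**The case against.** A reader might infer that the cost comparison as a whole loses most of its precision. The article does not support that. Costs are societal, and items such as primary care, informal care and productivity are not among the recorded outcomes, so their variance is the same either way. The article gives no hospital share, and at 30% the SE rises by only 12% to 14%.

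A reader might also take the 400 per time point to mean that two thirds of patients are missing. They are not: every patient supplies one follow-up form, so all 1200 per group contribute. The loss comes from the unobserved part of each patient's year.

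The best defence concerns the text itself. The article says that the RUM is used for the costs; it does not say that recorded admissions are excluded, and a full protocol or health-economic plan may draw on them. In a paragraph about questionnaires, following each patient may simply mean continuous form-filling. The article also cites methodological support for random cohorts. Much of this is fair, and it rules out saying that records will certainly go unused. But the paragraph names a single instrument for costs and gives a reason that, for readmissions, the article's own outcomes contradict. As that sentence frames it, the cited support is for sampling in place of continuous collection. It gives no reason to pass over a record that already covers the year.

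Three limits on the records also stand. Year-long medication capture is not shown for the control group, whose medication profile is described only at discharge. No time window is given for emergency visits or nursing home admissions. Coverage of other hospitals is not stated.

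**Conclusion.** The point holds for the hospital component. The economic section takes costs from the rotating RUM on a ground that does not apply to readmissions, which the trial follows for a year. For readmissions alone, the form-based estimate has about 2.2 to 4.7 times the variance of the full-year record (SE 0.023 to 0.033 against 0.0155). This rests on 3- to 6-month recall, 20% versus 15%, at most one readmission per patient and 1200 per group with complete forms. The other cohort layouts tried fall inside that range. Recall error and unreturned forms would come on top and cannot be sized from the article. The loss for total societal cost is smaller and its size is unknown, because it depends on the hospital share of cost variance. The effect analysis of readmission is unaffected.

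**What to change.** In Economic evaluation/ cost analysis:
- Value all study-hospital readmissions, with length of stay, from the electronic records of all randomised patients over the full year. Do the same for emergency visits and nursing home admissions as far as they are recorded over the year.
- Keep the rotating RUM for items the records do not hold, including care outside the study hospitals. Keep medication there too unless year-long capture in both groups is confirmed.
- Use RUM-reported study-hospital admissions only as a check, so that nothing is counted twice.
- Limit the statement that patients cannot be followed for a year to the questionnaire items, and state the RUM recall period.

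The cost is one further extract (length of stay) from systems already in use and some work to combine two sources. No new patient contact is needed.

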## Discussion

This study is expected to add evidence on the knowledge of medication optimization and whether continuous use of a CDSS ameliorates the risk of hospital readmission and other adverse outcomes in older patients who have already had an unplanned hospitalization.

Hospital (re)admissions place a significant burden on the healthcare system, with impact on quality of life from the patient perspective and being an important cost driver from the societal perspective. In earlier studies, different interventions have been investigated to reduce readmissions, but the results were inconclusive due to large heterogeneity in study designs and therefore their effect on hospital readmissions. As such, the optimal template of medication optimization is still unknown. This is the first study that includes patients with a high risk of having a medication-related admission based on the triggerlist. We deliberately chose to include all readmissions as primary outcome and not specifically medication-related readmissions because a clear definition is lacking. By using a suboptimal definition it is likely we would miss readmissions that later turn out to be medication-related.

To our knowledge, this is the first large randomized blinded study providing one-year follow-up data and reporting not only on quality of care indicators (readmissions), but also on quality-of-life and costs. This contrasts to other studies in the field, which usually have a follow up of 30 or 60 days at most. This is an important strength of our study, while we believe that in this population healthcare status and medication prescriptions alter frequently and a follow up of only 30 or 60 days is too short to identify all possible consequences and the time to the occurrence of adverse outcome might vary considerably. Another strength of this study is that it will be conducted in the outpatient setting and directly in daily clinical practice and therefore improves the possibility to implement the CDSS in the shortest possible notice. The inclusion of patients has already started in April 2019, but the patient inclusion was slower than expected due to different causes. The participation of GPs and pharmacists was lower than expected, we experienced several IT problems (not related to CDSS itself) that affected inclusion and from March 2020 we had to deal with the COVID-19 pandemic. As such, during many months the inclusion was discontinued.

In conclusion, we strongly believe that the continuous use of a CDSS reduces the number of hospital readmissions in older patients already at an increased risk of medication-related hospital admission. It is of vital importance to determine the optimal template of medication optimization and further improve this essential process to eventually achieve high-quality and cost-effective care, especially in older patients with polypharmacy.

## Data Availability

A de-identified dataset may be made available from the corresponding author on reasonable request once the study is completed.

## Abbreviations

CDSS: Clinical decision support system
CHECkUP: Control in the Hospital by Extensive Clinical rules for Unplanned hospitalizations in older Patients
EuroQol 5D-5L: EQ-5D-5L
GP: General practitioner
MAR: Missingness at random
MC: Medical Centre
MOP: Medication Optimization Profile
MUMC+: Maastricht University Medical Centre +
QALYs: Quality Adjusted Life Years
QoL: Quality of life
RUM: Resource Use Measurement
